**Intra-epidermal electrical stimulation**

- Characteristics of the psychophysical curve: nociceptive detection threshold and slope ( $A_{50}$  &  $\beta$ ).
- Intra-epidermal electrical stimulation evoked potentials (IESEP).

## 7 STUDY ASSESSMENTS

See **Table 1** (Part A) or **Table 2** (Part B) for the time points of the assessments.

### 7.1 Efficacy assessments

#### **On-the-road driving test**

Subjects will participate in validated on-road car driving tests. During these tests several safety precautions are taken to guarantee safety of the subjects and regular traffic. A licensed driving instructor (having access to dual controls) guards the safety of the subject and regular traffic during the test. In case the driving instructor or the subject is of the opinion that it is not safe to start or continue the driving test, the test will be interrupted. Subjects will operate a specially instrumented vehicle over a 55-km primary highway circuit, while maintaining a constant speed (95 km/h) and steady lateral position between the delineated boundaries of the right (slower) traffic lane. The subject will be allowed to deviate from this procedure only in order to overtake a slower vehicle traveling in the same traffic lane. The vehicle's speed and lateral position relative to the lane-lines is continuously recorded. These parameters are digitally sampled at 13 Hz by the MobilEye system (MobilEye Vision Technologies Ltd., Israel). Data is edited, off-line, to remove parts where data are disturbed by extraneous events (eg, passing maneuvers). SDLP (cm), ie, the weaving of the car, is the primary outcome variable. SDLP has been shown to be a sensitive measure to demonstrate dose-dependent differences from placebo for alcohol and psychoactive drugs including anxiolytics, antihistamines, antidepressants, hypnotics and analgesics, and drugs of abuse [4, 7, 25]. Standard Deviation of speed (SDS, km/h) will be a secondary variable. Mean lateral position (MLP, +/- cm), and mean speed (MS, km/h) are control variables. During screening, subjects will participate in a training driving test to become acquainted with the procedures of the driving test.

#### **Driving simulator test**

Simulated driving sessions will be conducted utilizing the Green Dino driving simulator developed by Green Dino BV, Wageningen, the Netherlands. This computer-based simulator system provides a realistic automotive driving environment, with 3 front channel displays, audio system, 3 pedals (clutch, brake, and gas) manual shift, full-size steering wheel, safety belt, indicators, and hand brake. The controls are linked to a dedicated graphics computer that simulates road environment and dynamic traffic. Subjects will be instructed to drive for 1/2 h with a steady lateral position in the right-lane in a dual-carriageway highway scenario. The driving simulator has been validated by CHDR in a study with subjects dosed with alprazolam or during alcohol clamp (0.5 and 1.0 g/dL; [data on file, CHDR, Leiden]). The SDLP was significantly affected after intravenous administration of both alcohol 0.5 g/L (1.9 cm) and 1.0 g/L (3.0 cm), and after oral administration of 1 mg alprazolam (5.6 cm).

#### **Perceived driving quality scale**

Immediately after each driving test, subjects will indicate the perceived quality of their driving performance on a visual analog scale from 0 ('I drove exceptionally poorly') to 20 ('I drove exceptionally well') around a midpoint of 'I drove normally' (see Appendix 1). The level of mental effort they had to invest in performing the task will be assessed on a 15 cm visual analogue scale with markings ranging from 'absolutely no effort' to over 'extreme effort'.

#### **Instructor assessment of driving quality**

Immediately after each driving test, the driving instructor will indicate the quality of driving performance during the instructor assessment. The assessment is structured with a matrix where aspects of driving receive a score between 1 and 10 (see appendix 2). The indication 'Not Applicable' will be used if there was no assessment possible of the driving aspect. Comments can be applied in the third column. The assessment will be done by the driving instructor and takes approximately 3 minutes.

**Karolinska Sleepiness Scale (KSS)**

Immediately before and after each driving test, the subject will complete the KSS, a Subject reported assessment used to rate sleepiness on a scale of 1 to 9, ranging from 'extremely alert' (1) to 'very sleepy, great effort to keep awake, fighting sleep' (9). See appendix 2 and appendix 3 for an example of the KSS.

**Leeds Sleep Evaluation Questionnaire (LSEQ)**

Leeds Sleep Evaluation Questionnaire [26] has 10 questions, the answers for which are captured on a VAS scale at the times indicated in the Time and Events Schedule. This clinical tool allows test persons to qualitatively assess their sleep. The LSEQ is electronically adapted in order to measure the correct medication effects. Only questions 8-14 will be analyzed, as questions 1-7 are related to IMP or medication use, which is not applicable in this study.

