#### **Questionnaires**

- Leeds Sleep Evaluation Questionnaire (LSEQ), questions 8-14.
- Karolinska sleepiness scale (KSS).

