## Appendix 7. Leeds Sleep Evaluation Questionnaire (English Version).

How would you compare getting to sleep using the medication with getting to sleep normally, i.e. without medication?

- |   |                             |       |                             |                                |
|---|-----------------------------|-------|-----------------------------|--------------------------------|
| 1 | Harder than usual           | _____ | Easier than usual           | GTS
Getting to sleep |
| 2 | Slower than usual           | _____ | Quicker than usual          |                                |
| 3 | Felt less drowsy than usual | _____ | Felt more drowsy than usual |                                |

How would you compare the quality of sleep using the medication with non-medicated (your usual) sleep?

- |   |                                        |       |                                         |                                |
|---|----------------------------------------|-------|-----------------------------------------|--------------------------------|
| 4 | More restless than usual               | _____ | More restful than usual                 | QOS
Quality of sleep |
| 5 | More periods of wakefulness than usual | _____ | Fewer periods of wakefulness than usual |                                |

How did your awakening after medication compare with your usual pattern of awakening?

- |   |                           |       |                    |                                     |
|---|---------------------------|-------|--------------------|-------------------------------------|
| 6 | More difficult than usual | _____ | Easier than usual  | AFS
Awake following sleep |
| 7 | Took longer than usual    | _____ | Shorter than usual |                                     |

How did you feel on waking?

- |   |       |       |       |                                          |
|---|-------|-------|-------|------------------------------------------|
| 8 | Tired | _____ | Alert | BFW
Behaviour following waking |
|---|-------|-------|-------|------------------------------------------|

How do you feel now?

- |   |       |       |       |
|---|-------|-------|-------|
| 9 | Tired | _____ | Alert |
|---|-------|-------|-------|

How would you describe your balance and co-ordination upon awakening?

- |    |                        |       |                        |

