## Appendix 8. Leeds Sleep Evaluation Questionnaire (Dutch Version).

Hoe zou u het in slaap vallen met het onderzoeksmiddel vergelijken met normaal in slaap vallen, d.w.z. zonder het onderzoeksmiddel?

- |   |                                        |       |                                             |                 |
|---|----------------------------------------|-------|---------------------------------------------|-----------------|
| 1 | Gemakkelijker dan gewoonlijk           | _____ | Moeilijker dan gewoonlijk                   |                 |
| 2 | Langzamer dan gewoonlijk               | _____ | Sneller dan gewoonlijk                      | GTS      |
| 3 | Ik voelde me slaperiger dan gewoonlijk | _____ | Ik voelde me minder slaperig dan gewoonlijk | Inslapen |

Hoe zou u de kwaliteit van het slapen met het onderzoeksmiddel vergelijken met uw normale slaap, d.w.z. zonder het onderzoeksmiddel?

- |   |                                                |       |                                                  |                            |
|---|------------------------------------------------|-------|--------------------------------------------------|----------------------------|
| 4 | Onrustiger dan gewoonlijk                      | _____ | Rustiger dan gewoonlijk                          | QOS                 |
| 5 | Meer periodes van wakker liggen dan gewoonlijk | _____ | Minder periodes van wakker liggen dan gewoonlijk | Kwaliteit van slaap |

Hoe was het wakker worden na het onderzoeksmiddel vergeleken met uw gebruikelijke patroon van wakker worden?

- |   |                                  |       |                                  |                 |
|---|----------------------------------|-------|----------------------------------|-----------------|
| 6 | Moeilijker dan gewoonlijk        | _____ | Makkelijker dan gewoonlijk       | AFS      |
| 7 | Het duurde langer dan gewoonlijk | _____ | Het duurde korter dan gewoonlijk | Ontwaken |

Hoe voelde u zich bij het wakker worden?

- |   |          |       |       |  |
|---|----------|-------|-------|--|
| 8 | Vermoeid | _____ | Alert |  |
|---|----------|-------|-------|--|

Hoe voelt u zich nou?

- |   |          |       |       |  |
|---|----------|-------|-------|--|
| 9 | Vermoeid | _____ | Alert |  |
|---|----------|-------|-------|--|

Hoe was uw evenwichts- en coördinatiegevoel bij het opstaan?

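### The LSEQ endpoint is set as questions 8-14, but the appended form ends at 10, and two of its three remaining items ask about waking, which has no defined meaning after a night awake

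*Protocol*

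**What the plan says.** Protocol section 7.1, under the LSEQ heading, states "Leeds Sleep Evaluation Questionnaire [26] has 10 questions". It adds that the questionnaire has been adapted electronically, and then says "Only questions 8-14 will be analyzed, as questions 1-7 are related to IMP or medication use". Section 6.2 lists the endpoint for Part A as "Leeds Sleep Evaluation Questionnaire (LSEQ), questions 8-14" and repeats the entry for Part B.

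Appendix 7 (English) and Appendix 8 (Dutch) print the form, and both stop at item 10. Items 1-7 stand under headings that mention the medication. The other three are:

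- Item 8: "How did you feel on waking" (Dutch: "Hoe voelde u zich bij het wakker worden")
- Item 9: "How do you feel now"
- Item 10: "How would you describe your balance and co-ordination upon awakening" (Dutch: "Hoe was uw evenwichts- en coördinatiegevoel bij het opstaan", which asks about getting up)

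Tables 1 and 2 mark the questionnaires, LSEQ included, in the sleep-deprived column. Section 3.1 has subjects awake for the whole night before that morning's assessments. Section 9.9 estimates the difference between the sleep and sleep-deprived states with a mixed model, and section 1.2.6 counts all parameters related to sleep deprivation as main endpoints.

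**The concern.** There are two problems, and the second depends on how the first is resolved.

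First, the item range does not fit the form. The range appears three times (6.2 Part A, 6.2 Part B and 7.1), so it is not an isolated slip in one place. A programmer working from the protocol cannot tell which items make up the endpoint.

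Second, if the appended form is the one in use, two of the three items left after dropping 1-7 ask how the subject was on waking or getting up. The rested subject has such a moment that morning and the sleep-deprived subject does not. The protocol gives no rule for answering these items after a night awake. A difference between states on them could reflect how subjects reinterpreted the question, yet appear in the results as an effect of sleep deprivation.

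**Working it through.** No sample size, power or error rate enters this point. The check is an item count followed by a comparison of wording.

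**Item count**

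| Quantity | Source | Result |
|---|---|---|
| Questions on the form, as stated | 7.1 | 10 |
| Questions on the form, as printed | Appendices 7 and 8 | items 1 to 10, i.e. 10 |
| Question numbers to be analysed | 6.2, 7.1 | 8 to 14: 14 − 8 + 1 = 7 |
| Named and on the form | intersection | 8, 9, 10: 3 items |
| Named but not on the form | remainder | 11, 12, 13, 14: 7 − 3 = 4 |

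The stated count of 10 agrees with both appendices. The analysed range does not agree with either.

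**Does the stated reason identify the form?** Section 7.1 drops items 1-7 because they concern medication. On the printed form, the headings over items 1-7 name the medication and those over 8-10 do not. The lower end of the range therefore fits the appended form; only the upper end runs past it. This is compatible with 14 being an error for 10. It does not rule out an electronic form with further items, because the protocol gives no item list for that version.

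**Meaning of the three items in each state, on the appended form**

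| Item | Rested morning | Morning after a night awake |
|---|---|---|
| 8, feeling on waking | that morning's waking | no such waking |
| 9, feeling now | present moment | present moment |
| 10, balance on awakening (Dutch: on getting up) | that morning | no such moment |

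Two of three items lack a referent in one state, leaving 3 − 2 = 1 item with the same meaning in both.

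**What the planned contrast then estimates.** With complete pairs, the section 9.9 model estimates the mean of (deprived − rested) within subject. For item 9 this is the change in current alertness. For items 8 and 10 it depends on what the sleep-deprived subject does:

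- If all leave the item blank, one state has no data and the contrast cannot be estimated.
- If some leave it blank, missingness depends on the state being compared. Section 9.4 rules out imputing missing results but relies on the mixed model to estimate missing values.
- If they rate an earlier morning's waking, the contrast compares one waking after sleep with another.
- If they rate the present moment, it compares waking with now.

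None of these is the effect of sleep deprivation on the quantity the item asks about.

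**The case against.** The strongest reply is that 7.1 mentions an electronic adaptation which is not shown. If 8-14 is that version's numbering, the analysed items need not be the printed 8, 9 and 10, and the remarks about waking may concern the wrong questions. This stands as a limit: the comparability problem is conditional on the appended form being the one used. It does not remove the numbering problem, because in that case the statement of 10 questions and the two appendices would not describe the form in use.

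A second reply is that if 14 is simply a slip for 10, the endpoint can be computed from items 8-10. That is correct. A reader might infer that the endpoint cannot be computed at all; the documents do not support that.

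A reader might also suppose that the three items are averaged, so that two-thirds of a score rests on waking questions. The protocol specifies no LSEQ composite. The behaviour-following-waking label in the appendices is only a printed domain name, and section 9.1 leaves derivation algorithms to the SAP. Analysed item by item, item 9 is untouched by 8 and 10.

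Third, subjects can still mark the line, and the Dutch item 10 is looser because it asks about getting up. So the items are not literally unanswerable. They lack a defined referent after a night awake, which is enough to spoil the comparison between states.

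Finally, the study is exploratory, the LSEQ is not named in the objectives, and the sample size rests on simulator SDLP and the cold pressor test. That limits the weight of the point. It is no reason to leave the definition wrong, given that section 1.2.6 counts all related parameters as main endpoints.

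**Conclusion.** The concern holds in two steps. Without conditions, the range 8-14 contradicts the 10-question form described in 7.1 and printed in both appendices: four of the seven numbers named do not exist there. On the assumption that the appended form is the one administered, items 8 and 10 have no defined referent in the sleep-deprived state, so only one of the three existing items supports the planned contrast.

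The consequence is confined to the LSEQ. Nothing here affects the power calculation or any other endpoint. Nor do the documents support a claim that a misleading result would be presented as coming from a validated scale: section 7.1 calls the LSEQ a clinical tool and does not describe it as validated. The size of any distortion cannot be given, because the protocol does not say how subjects are to answer waking questions after no sleep.

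**What to change.** In section 6.2 (both parts) and section 7.1:

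1. Reconcile the count of 10 with the range 8-14. If the electronic form is numbered differently, append it and correct the count and the appendices to match.
2. Name the analysed items by their wording, so that the definition no longer depends on numbering.
3. Restrict the sleep versus sleep-deprived contrast to items about the present moment, which is item 9 on the appended form. If another form applies, select items by the same rule.
4. Report waking items descriptively, for the rested state only. They need not be withheld from subjects; keeping them out of the contrast is enough.

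The cost is a change of wording. On the appended form, two VAS items leave the contrast. Little is lost, since KSS and the Bond-Lader alertness score are endpoints in both parts and still cover sleepiness.

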**Adaptive tracking**

The adaptive tracking test will be performed as originally described by Borland and Nicholson [27] using customized equipment and software (based on Tracker USB hard-/software (Hobbs, Hertfordshire, UK)). The average performance and the standard deviation of scores over a 3.5-minute period will be used for analysis. This 3.5-minute period is including a run in time of 0.5 minute, in this run in time the data is not recorded. Adaptive tracking is a pursuit-tracking task. A circle moves randomly about a screen. The subject must try to keep a dot inside the moving circle by operating a joystick. If this effort is successful, the speed of the moving circle increases. Conversely, the velocity is reduced if the test subject cannot maintain the dot inside the circle. Each test is preceded by three training sessions and includes two baseline measurements. After 3 practice sessions, learning effects are limited. The adaptive tracking test is more sensitive to impairment of eye-hand co-ordination by drugs than compensatory pursuit tasks or other pursuit tracking tasks, such as the pursuit rotor. The adaptive tracking test has proved to be useful for measurement of CNS effects of alcohol, various other psychoactive drugs and sleep deprivation [1, 28]. The recording of tracking performance will take approximately 5 minutes.

**Body Sway**

The body sway meter allows measurement of body movements in a single plane, providing a measure of postural stability. Body sway is measured with a pot string meter (celesco) based on the Wright ataxia meter [29]. At CHDR, the method has been used to demonstrate effects of sleep deprivation [2], alcohol [30], benzodiazepines [2, 31] and other psychoactive agents (data on file). With a string attached to the waist, all body movements over a period of time are integrated and expressed as mm sway. Subjects will be instructed to wear a pair of comfortable, low-heeled shoes on each session. Before starting a measurement, subjects will be asked to stand still and comfortable, with their feet approximately 10 cm apart and their hands in a relaxed position alongside the body and eyes closed. Subjects may not talk during the measurement. The total period of body-sway measurement will be two minutes.

**Saccadic eye movements**

Saccadic peak velocity is one of the most sensitive parameters for sedation [2, 28, 32]. The use of a computer for measurement of saccadic eye movements was originally described by Baloh et al. [33], and has been validated at CHDR by Van Steveninck et al. [28, 32]. While the sedative effects of 20 mg oral temazepam were detectable by subject self-report, visual analogue scales and SEM testing, at a dose of 5 mg were only detectable with measures of SEM [34]. The effects of 1 night of sleep deprivation (suggested as a threshold level of clinically significant sedation) were consistently detectable by SEM with a sustained decrease in saccadic peak velocity of 9 to 10% observed [2]. Saccadic eye movements will be recorded at a training session, pre-dose and at times specified in the protocol. Recording of eye movements will be performed in a quiet room with dimmed lightning. There will be only one subject per session in the same room.

Recording and analysis of saccadic eye movements is conducted with a microcomputer-based system for sampling and analysis of eye movements. The program for signal collection and the AD-converter is from Cambridge Electronic Design (CED Ltd., Cambridge, UK), the amplification by Grass (Grass-Telefactor, An Astro-Med, Inc. Product Group, Braintree, USA) and the sampling and analysis scripts are developed at the CHDR (Leiden, the Netherlands). Disposable silver-silver chloride electrodes (Ambu Blue Sensor N) will be applied on the forehead and beside the lateral canthi of both eyes of the subject for registration of the electro-oculographic signals. Skin resistance is reduced to less than 5 kOhm before measurements. Head movements are restrained using a fixed head support. The target consists of a moving dot that is displayed on a computer screen. This screen is fixed at 58 cm in front of the head support.

Saccadic eye movements are recorded for stimulus amplitudes of approximately 15 degrees to either side. Fifteen saccades are recorded with interstimulus intervals varying randomly between 3 and 6 seconds. Average values of latency (reaction time), saccadic peak velocity of all correct saccades and inaccuracy of all saccades will be used as parameters. Saccadic inaccuracy is calculated as the absolute value of the difference between the stimulus angle and the corresponding saccade, expressed as a percentage of the stimulus angle.

### **Smooth pursuit eye movements**

The same system as used for saccadic eye movements is also used for measurement of smooth pursuit. For smooth pursuit eye movements, the target moves at a frequency ranging from 0.3 to 1.1 Hz, by steps of 0.1 Hz. The amplitude of target displacement corresponds to 22.5 degrees eyeball rotation to both sides. Four cycles are recorded for each stimulus frequency. The method has been validated at CHDR by Van Steveninck et al. [32] based on the work of Bittencourt et al. [34] and the original description of Baloh et al. [33]. The time in which the eyes are in smooth pursuit of the target will be calculated for each frequency and expressed as a percentage of stimulus duration. The average percentage of smooth pursuit for all stimulus frequencies will be used as parameter. The measurements of smooth pursuit eye movements will take approximately 3 minutes.

### **VAS Bond and Lader**

VAS as originally described by Norris have often been used previously to quantify subjective effects of a variety of sedative agents [35, 36]. Dutch versions of the scales have been frequently employed at CHDR for a variety of sedative agents [28] and circumstances [36]. At each time point of assessment the subject indicates (with a mouse click on the computer screen) on 16 horizontal VAS how he/she feels. The 16 measurements are recorded in the subject's eCRF. From these measurements, three main factors are calculated as described by Bond and Lader [37]: alertness (from nine scores), mood (from five scores), and calmness (from two scores). The VAS are provided in Appendix 4 (Dutch version) and Appendix 5 (original English version). Completing the set of VAS will take approximately 2 minutes.

